#### Objective 4 considerations

A sample of 6 clinics will be selected, including 3 high- and 3 low-implementing clinics as identified by their clinic referral rate, enrollment rate, and mean attendance. Samples of participants will be drawn from each of the 6 clinics. To ensure that the data reflect the diversity of roles and experiences, we will use purposive sampling to include caregivers, clinicians, and PriCARE/*CARIÑO* facilitators. Caregiver sampling will be balanced by language and number of sessions attended (<3 or >3). Clinician sampling will be balanced to include those with high and low referral rates. Altogether, we anticipate interviewing 3–5 caregivers per site (18–30 total), 2–3 clinicians per site (12–18 total), and 10 PriCARE/*CARIÑO* facilitators. We anticipate this will provide sufficient data to achieve saturation relative to our primary objectives of identifying factors that may be implementation determinants (objective 4) and contextualizing the quantitative analyses of mechanisms of change (objective 3) [89].

#### Objective 5 considerations

Pre- and post-intervention ECBI scores for 483 enrolled dyads (randomized 1:1) studied during a time of virtual delivery of the PriCARE/*CARIÑO* intervention will be compared to historical scores from 444 dyads (randomized 1:1) previously studied in three trials during in-person delivery. The observational cohort-comparison study may be subject to confounding biases. The analyses will be descriptive with a focus on point and interval estimates of means, mean changes, differences, and variance components. In terms of the ECBI pre- vs post-intervention change score, a 10-unit difference between the two regimens will be considered clinically important.

### Recruitment {15}

The study team will be made aware of potential participants in 3 ways: (1) A point-of-care alert in the EMR will prompt physicians to inform caregivers at eligible well child visits about the PriCARE/*CARIÑO* study and if the caregiver provides verbal permission to be contacted by study staff, a referral message will be sent to the study team (Fig. 3); (2) Clinic providers will obtain verbal permission from the caregiver to be contacted by study staff and notify the study team of the caregiver contact information in-person, via EMR message, via EMR order, email, or phone; (3) The interested caregiver may contact the study team directly by email or phone using the study team’s contact information provided on the recruitment flyer, which will be posted in the waiting room and in exam rooms and included in well child visit packets.

**Fig. 3 Fig3:**
[figure not shown]
PriCARE electronic medical record alert that reminds clinicians to refer eligible patients during well child visits

## Assignment of interventions: allocation

### Sequence generation {16a}

Enrolled dyads will be assigned by 1:1 stratified randomization to PriCARE/*CARIÑO* plus usual care or to usual care alone. The randomization schedule, stratified by *clinical site* and *language*, will be generated using permuted blocks of sizes 2 and 4 in an unpredictable order. This means that prior to the start of recruitment we will have created two separate allocation tables for each clinical site. Each allocation table will be sufficiently extensive to accommodate an unexpectedly large cohort. The allocation tables will be concealed from the study personnel during the study.

### Concealment mechanism {16b}

The collection of site-and-language-specific allocation tables will be uploaded to the REDCap database prior to study initiation. A feature of the REDCap database will be used to conceal the treatment assignments from the study team until the moment the newly enrolled caregiver-child dyad is ready to be assigned to a regimen.

### Implementation {16c}

During recruitment, a Study ID number will be assigned to each dyad. Screening for eligibility will be conducted by phone after verbal informed consent to be screened is obtained. Eligible dyads who wish to enroll will provide written informed consent to study participation and complete the first REDCap data collection survey. The REDCap randomization tool will be used to assign the enrolled dyad to a treatment regimen: a study team member will click on the “randomize” field to reveal the allocation and notify the caregiver of their treatment regimen.

## Assignment of interventions: blinding

### Who will be blinded {17a}

Due to the nature of the intervention, subjects cannot be blinded to regimen allocation but will be instructed not to disclose their allocation status at the follow-up assessments. Regarding the primary outcome, CPS investigations of suspected CM, CPS agencies, and administrators recording reports and preparing data files with CPS data for the study team will be blind to treatment allocation. With regard to the secondary outcomes, baseline interviews will occur prior to randomization and all follow-up data collection will be conducted by an assessor blind to treatment allocation. For each member of the study team, REDCap data entry and access privileges will be personalized to the role of the individual such that team members will only be able to view/access specific fields within records in order to maintain blinding.

### Procedure for unblinding if needed {17b}

Given that subjects are already unblinded to treatment allocation, a procedure for further unblinding is not applicable as we anticipate no situation in which unblinding of study team members will be necessary.

## Data collection and management

### Plans for assessment and collection of outcomes {18a}

The Research Data Capture (REDCap) software system will be used to create and manage the study databases. Multiple streams and types of data will be collected including CPS investigations, surveys with a REDCap user interface, caregiver-child observations, qualitative interviews, attendance data, and data regarding intervention referrals, eligibility, enrollment, and fidelity.

#### CPS investigations

Through Data Use Agreements with the relevant CPS agencies, the research team will provide a matching dataset to CPS containing caregiver and child demographic information required for matching and the start and end date for CPS data matching for each dyad. Using this information, a coded dataset, purged of child and caregiver identifiers, containing study ID and data on investigated reports (report date, allegation type, investigation outcome) occurring during the CPS data matching period will be created for the study. The CPS dataset will be merged with a coded dataset containing demographic and survey data from REDCap but purged of PHI. The two datasets will be merged on the study ID number, and then fully de-identified for final analysis.

#### REDCap enabled surveys

Trained research coordinators will collect survey data via phone or videoconference at baseline (0 months) and at follow-up (6–8 months). The caregiver may also choose to complete the survey online. The surveys will include information on demographic characteristics, potential moderators (caregiver mental illness and caregiver history of childhood trauma), and measurements of outcomes of interest detailed in Table 1. Participants will be compensated $40 for each REDCap survey.

#### Caregiver-child observations

In addition to the caregiver-reported survey data, 120 dyads will complete the DPICS at baseline and at follow-up (6–8 months). Starting in year 3 of the study, we will consecutively administer the DPICS until 120 dyads have completed both the baseline and follow-up DPICs. Participants will be compensated $20 and a toy for each DPICS.

#### Qualitative Interviews

Qualitative interviews will be conducted with caregivers randomized to PriCARE/*CARIÑO*, referring clinicians, and PriCARE/*CARIÑO* facilitators from 3 low-implementing and 3 high-implementing clinics. TDF will inform interview guide development and transcript coding and analysis. TDF is an integrated theoretical framework with 14 domains that focus on the cognitive, affective, social, and environmental influences on behavior [78, 79]. The research team will select the most relevant domains to the behaviors of interest (referrals, enrollment, and attendance) in designing the interview guide. The goals of the interviews include: (1) examine implementation determinants and characterize strengths and barriers across settings; (2) solicit feedback regarding lessons learned and best practices to support wide-based dissemination and implementation; and (3) identify perceived mechanisms of change of the intervention itself. Participants will be compensated $20 for each interview.

#### Intervention referral, enrollment, and attendance

Clinician referrals to PriCARE/*CARIÑO* from the EMR alert and the number of patient encounters in which the EMR alert was active will be used to calculate clinic referral rates which will be stored in the REDCap database. Enrollment and attendance will be recorded by research coordinators and will be used to calculate clinic means. Data will include the number of referred dyads who enroll in the study and the number of sessions attended by each caregiver randomized to PriCARE/*CARIÑO*.

### Plans to promote participant retention and complete follow-up {18b}

The reasons for missing data values will be documented in the REDCap database. We will attempt to follow up all enrolled participants, even if they withdraw from their assigned regimen.

Caregiver retention in the study will be promoted as follows: (1) compensate dyads immediately following data collection; (2) obtain multiple phone numbers, email addresses, and mailing addresses from dyads upon enrollment to ensure the ability to contact for follow-up data collection; (3) call/email all contact information multiple times at different times of the day to complete follow-up data collection interview; (4) provide multiple time/date options and modalities (phone, virtual, online self-administered, in-person) to complete data collection; (5) provide direct study team phone number for study participants to call or text with study questions or to schedule study interviews.

### Data management {19}

Multiple features will ensure both the integrity and validity of the collected data. Referral, enrollment, attendance, fidelity, DPICS codes, and caregiver interview data will be entered and stored in electronic REDCap databases.

The caregiver survey data will be directly entered into the data collection form thereby eliminating risk of errors in the transposition of data. REDCap provides real-time validation rules (with automated data type and range checks), easy data manipulation (with audit trails for reporting, monitoring, and querying subject records), and an automated export mechanism to common statistical packages. Team members involved with data entry will undergo extensive training on the study database and best practices for data entry including mock data entry trainings.

Video recordings, audio recordings, and interview transcripts will be stored on a secure password-protected server. As qualitative data collection progresses, the study team will review interview transcripts to assess data quality and ensure the content collected meets our study aims.

De-identified data from CPS will be stored on a secure password-protected server. After all data collection is completed, the CPS data will be merged with the REDCap data on the study ID. The study ID will be replaced with a new randomly generated unique identifier that cannot be traced back to the REDCap data. The de-identified, coded dataset will be used for analysis.

### Confidentiality {27}

All data and confidential study files will be stored in (1) a secure, web-based data application (REDCap) that is password protected so that only study team members granted privileges will have access or (2) single sign-on secure access networks in study-specific folders accessible only to study team members. All personal identifying information will be removed before a de-identified finalized, merged dataset for analysis is provided to the statistical team.

### Plans for collection, laboratory evaluation, and storage of biological specimens for genetic or molecular analysis in this trial/future use {33}

Biological specimens will not be obtained in this trial.

## Statistical methods

### Statistical methods for primary and secondary outcomes {20a}

#### Analysis plans for objective 1

##### Evaluation of effectiveness

For the primary analysis of the proportion of children with at least one CPS investigation during follow-up, we will use a logistic regression model with covariate adjustment for the length of follow-up (log_10_ months). To account for the clustering of dyads within clinical sites and within small groups of 8-10 for PriCARE sessions, the model will be fitted using generalized estimating equation (GEE) methods with robust standard error estimates. *Clinical site* will be treated as a random effect. To improve precision of the estimators of *regimen*-specific treatment effects, caregiver *language* (Spanish speaking) will be included as a covariate. This model assumes that the difference between regimens is not a function of *language*. The population parameters (estimands [90]) of interest are the regression coefficients, the regimen-and-language-specific proportions that would be expected during 12–48 months of follow-up, and the treatment effect (expected difference between proportions) along with its odds ratio. The point estimates and 95% CI estimates for these estimands will be presented graphically in a figure using a forest-plot format. The p-value for the treatment effect will be shown to four decimal places and will be interpreted as a continuous score [91–93]. The *S*-value = log_2_ (^1^/_*p* value_) representing the available amount of information (Shannon information) against the null hypothesis “the treatment effect is exactly zero” will also be shown in the figure.

##### Effectiveness as a function of language

A *regimen*-by-*language* interaction term will be added to the above model to allow evaluation of intervention effectiveness as a function of *language*. A forest plot figure will display point and interval estimates for the estimands: proportions, differences of proportions, and the two language-specific treatment effects and their difference along with odds ratios. *P*-values and *S*-values for the two treatment effects and for their difference will be included in the figure to address (null) hypotheses such as “among Spanish-speakers the treatment effect is zero,” “both treatment effects are zero,” and “the two treatment effects are exactly the same (no effect-modification).”

##### Hypothesis generation/refinement

To enhance understanding of the main results (above) and to explore the roles of other covariates, we will explore numerous versions of the logistic model. These will include additional covariates measured prior to randomization such as the child (e.g., age, gender, race, ethnicity) and caregiver (e.g., age, gender, race, ethnicity, education, number of children) demographic variables, and caregiver scores (e.g., PHQ9, GAD7, ACEs). Moderating effects of these covariates will be investigated by including interaction terms such as PHQ9-by-regimen, GAD7-by-regimen, and ACEs-by-regimen. Overfitting bias due to inclusion of too many covariates will be avoided in these exploratory model-building efforts. We anticipate observing at least 200 “cases” (children with one or more CPS investigation) which is sufficient to support the fitting of this model with 10 fixed-effect coefficients representing independent variables. If 300 cases occur, then the logistic model would support up to 15 coefficients.

#### Analysis plans for objective 2

##### Evaluation of effectiveness

For each of the secondary outcome variables (BCAP, CTS-PC, ECBI, PSI-SF, PS, DPICS) the analyses will rely on a generalized linear model with GEE estimation. The dependent variable will be the change score computed as the follow-up score (at 6–8 months post-randomization) minus the baseline score. The independent variables will be *regimen* and *language* (Spanish-speaking). *Clinical site* will be treated as a categorical random effect. The estimands of interest are mean levels of the scores. The analysis strategies will be very similar to those described above in the “Analysis plans for objective 1” section. Point and interval estimates of the estimands will be presented graphically in forest plot figures.

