#### Objective 2 outcome measures

CM risk, harsh, neglectful, and dysfunctional parenting, child behavior problems, caregiver stress, and caregiver-child interactions (*n*=120) will be measured prior to randomization and 6-8 months later. The anticipated result is that the intervention will improve these scores to varying degrees. See Table 1 and Fig. 2 for data collection timeline.

**Table 1 Tab1:** Schedule of evaluations for quantitative objectives 1–3

Variables measured	Obj 1	Obj 2	Obj 3	Instrument	Occasions (months)		
					0	6–8	4–52
Demographics	Covariates	Covariates	Covariates	Self-report for caregiver and child	✓		
Spanish-speaking	Covariate	Covariate	Covariate	Self-report for caregiver	✓		
Caregiver depression	Moderator	Moderator		Patient Health Questionnaire-9 (PHQ-9)	✓		
Caregiver anxiety	Moderator	Moderator		General Anxiety Disorder-7 (GAD-7)	✓		
Caregiver ACEs	Moderator	Moderator		Adverse Child Experiences (ACE)	✓		
Child behavior problems		Dependent	Mediator	Eyberg Child Behavior Inventory (ECBI)	✓	✓	
Harsh parenting		Dependent	Mediator	Conflict Tactics Scales, Parent-Child version (CTS-PC)	✓	✓	
Dysfunctional parenting		Dependent	Mediator	Parenting Scale (PS)	✓	✓	
Caregiver-child interactions^b^		Dependent		Dyadic Parent-Child Interaction Coding System (DPICS)	✓	✓	
Caregiver stress		Dependent	Mediator	Parenting Stress Index-Short Form (PSI-SF)	✓	✓	
Maltreatment risk		Dependent	Dependent	Brief Child Abuse Potential Inventory (BCAP)	✓	✓	
Child maltreatment^**a**^	Dependent		Dependent	Child Protective Services (CPS) investigation			✓

^a^The length of follow-up data collection for CPS investigations will vary by participant depending on time of enrollment but will be up to 48 months (52 months after enrollment)

^b^Recorded for a subsample of 120 dyads

*CM risk will be measured by the Brief Child Abuse Potential Inventory (BCAP)*, a questionnaire that measures CM risk and includes a 34-item Child Physical Abuse scale [60]. The two internal validity scales can be used to create validity subtests: lie and random response [60]. BCAP is a brief version of the Child Abuse Potential Inventory and on cross-validation, BCAP risk scale scores demonstrated an internal consistency of 0.89 and substantial correlation with the Child Abuse Potential Inventory abuse risk score (r=0.96) [60, 61].

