*Harsh and neglectful parenting will be measured by the Conflict Tactics Scales, Parent-Child version (CTS-PC)*, a 35-item scale focusing on the respondent’s behavior with their child including discipline methods. In this study, we will include the 18 items that constitute the nonviolent discipline, psychological aggression, and corporal punishment subscales [62–64]. We will not include the neglect, sexual abuse, physical assault, or physical maltreatment subscales of the CTS in order to minimize the potential legal risk to caregivers related to mandatory reporting laws. Reliability coefficients are moderate, with alpha coefficients of 0.70 for nonviolent discipline, 0.68 for psychological aggression, and 0.72 for corporal punishment [62–64]. The CTSPC has adequate discriminant and construct validity [62, 63]. Test-retest reliability has been established with a correlation of 0.8 at 5 months [62].

*Dysfunctional discipline will be measured by the Parenting Scale (PS)*, a 30-item self-report questionnaire designed to assess dysfunctional parenting discipline strategies including laxness (permissive inconsistent discipline, providing positive consequences for misbehavior), over-reactivity (harsh, emotional, authoritarian discipline characterized by irritability), and hostility (use of verbal or physical force). The PS has demonstrated adequate psychometric properties including internal consistency, test-retest reliability, and convergent validity with other validated measures, and is correlated with observational measures of inadequate parental discipline and child misbehavior [65–67].

*Child behavior problems will be measured by the Eyberg Child Behavior Inventory (ECBI)*, a 36-item parent survey used to assess the current frequency and severity of disruptive behaviors at home in children 2–16 years [68]. The test-retest reliability of the ECBI has been established with correlations near 0.75 for both subscales over a 10-month interval [69]. ECBI scores are highly correlated with observational measures of child negative affect, non-acceptance, and dominance [70]. The ECBI is also correlated with other measures of child behavior problems (has convergent validity) and conversely the ECBI has high discriminant validity. The ECBI is a sensitive indicator of intervention efficacy/effectiveness [71, 72].

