Interviews will continue until thematic saturation is reached. Transcribed interviews will be analyzed using qualitative content analysis, a theory-driven approach [95, 96]. This coding approach is both deductive (codes are derived from TDF) and inductive (codes are derived from the data). The goals of the analyses will be to identify barriers and facilitators associated with implementation, to identify targeted implementation strategies that can be evaluated in a future trial, and to identify potential mechanisms of intervention-induced change.

#### Analysis plans for objective 5

The ancillary study will be conducted when 483 enrolled caregiver-child dyads (randomized 1:1) have completed the 6-month follow-up interview. Pre- and post-intervention ECBI scores for 483 enrolled dyads (randomized 1:1) studied during a time of virtual delivery of the PriCARE/*CARIÑO* intervention will be compared to historical scores from 444 dyads (randomized 1:1 or 2:1) previously studied in 3 trials during in-person delivery. As in the case of objective 2, the analyses will rely on a generalized linear model with GEE estimation. The dependent variable will be the ECBI change score computed as the 6-month follow-up score minus the baseline score. Participants lost to follow-up will have missing values. The independent variables will be *treatment regimen* (intervention, control) and *clinical site*. Point estimates with 95% CI estimates will be obtained for the population parameters of interest: total variance, mean change for each regimen, the difference between the two mean changes. The treatment-effect estimates will be presented graphically in forest plot figures. Comparable results will be obtained using the dyad-level data from each of the 3 previous trials. To obtain point and interval estimates of differences among the four studies, the generalized linear model will be expanded to include data from all 4 studies along with use of terms in the regression equation representing *study* and *study*-by-*regimen* interaction. The means and mean differences of interest include those that address regimens, studies, differences between regimens (i.e., treatment effects), and differences between studies. The various study-specific estimates of means, mean differences, and variances will be presented graphically in forest plot figures.

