### Methods for additional analyses (e.g., subgroup analyses) {21b}

#### Sensitivity analyses objective 1

To guide our level of trust in the main results about effectiveness, sensitivity analyses will be used to evaluate the robustness/fragility of the main results to reasonable perturbations of the assumptions and statistical methods used; for example, examination of the impact of (1) including/excluding questionable data, (2) representing PriCARE exposure in terms of the number of attended PriCARE sessions (dose) instead of intent-to-treat allocation, (3) excluding caregivers assigned to PriCARE who attended ≤ 3 of the 6 sessions, (4) using a generalized logistic mixed-effects model, (5) using a generalized log-linear model for the binary outcome (CPS investigation yes/no) or for the dyad’s number of CPS investigations, (6) using a Cox proportional hazards model for time to first CPS investigation. The sensitivity analyses will only be used to guide our level trust in the main results and guide wording of our conclusion statements.

#### Sensitivity analyses objective 2

To guide our level of trust in the main results about effectiveness, sensitivity analyses will be used to evaluate the robustness/fragility of the main results to reasonable perturbations of the assumptions and statistical methods used; for example, examination of the impact of (1) including/excluding questionable data, (2) using a constrained longitudinal generalized linear model which would be able to include all subjects—even those without follow-up data at 6–8 months, (3) representing PriCARE exposure in terms of the number of attended PriCARE sessions (dose) instead of intent-to-treat allocation, (4) excluding caregivers assigned to PriCARE who attended ≤ 3 of 6 sessions.

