### Methods in analysis to handle protocol non-adherence and any statistical methods to handle missing data {20c}

For the main analysis, we will assume that any missing data values were caused by ignorable mechanisms [97]. Additional sensitivity analyses will be used as described in {20b}.

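### Objective 2's main models analyse raw change scores in completers without the baseline score as a covariate, which costs about 10–12.5% of variance on CTS-PC and ECBI

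*Protocol article*

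**What the plan says.** All references are to the protocol article.

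- **Main secondary model** (Analysis plans for objective 2, Evaluation of effectiveness). For BCAP, CTS-PC, ECBI, PSI-SF, PS and DPICS: "The dependent variable will be the change score computed as the follow-up score (at 6–8 months post-randomization) minus the baseline score". The covariates follow: "The independent variables will be *regimen* and *language* (Spanish-speaking"), with site as a random effect and GEE estimation. The baseline score is not among them.
- **Baseline data** (Objective 2 outcome measures). The scores "will be measured prior to randomization and 6-8 months later", so the covariate is already collected. DPICS is recorded in 120 dyads only.
- **Dropout** (Objective 2 considerations; section {20c}). A 10% loss is expected at the follow-up interview. The main analysis assumes that "any missing data values were caused by ignorable mechanisms".
- **Sensitivity analysis** (Sensitivity analyses objective 2). One listed option is "using a constrained longitudinal generalized linear model which would be able to include all subjects", including those with no follow-up score.
- **Objective 5** (Analysis plans for objective 5). The same approach is used: "The dependent variable will be the ECBI change score computed as the 6-month follow-up score minus the baseline score", with regimen and site as independent variables.
- **Correlation over time** (Objective 2 outcome measures). For ECBI the article cites "correlations near 0.75 for both subscales over a 10-month interval". For CTS-PC it cites 0.8 at 5 months.

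**The concern.** In a randomised comparison, a change score fixes the coefficient of the baseline at 1. Adjusting for the baseline lets the data choose that coefficient. In large samples the adjusted analysis is never less precise, and it does not carry chance baseline imbalance into the estimate through regression to the mean. The article collects the baseline and then leaves it out of the covariate list. This is a stated choice of main model, not a detail left to an analysis plan.

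The second issue is consistency with the missing-data assumption. Ignorable missingness allows dropout to depend on the observed baseline score. A completer analysis of change that does not condition on baseline is not generally valid under that assumption. The model that is valid is listed, but only as a sensitivity analysis.

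At stake are wider intervals than necessary for every secondary score and a small, avoidable exposure to bias in the interview-based outcomes.

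**Working it through.** The article states no power or precision figure for objective 2, so there is none to reproduce. The calculations ignore clustering.

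**1. Precision.** Let s0 and s1 be the SDs at baseline and follow-up, and r their correlation within arm.

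- Variance of change: s0² + s1² − 2·r·s0·s1
- Variance after baseline adjustment: s1²(1 − r²)
- Difference: (s0 − r·s1)², which is never negative

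With s0 = s1 the ratio of adjusted to change-score variance is (1 − r²)/[2(1 − r)] = (1 + r)/2.

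| Measure | r | Ratio | Variance saved | Extra dyads needed by change score |
|---|---|---|---|---|
| PSI-SF | 0.84 | 0.920 | 8% | 8.7% |
| CTS-PC | 0.80 | 0.900 | 10% | 11.1% |
| ECBI | 0.75 | 0.875 | 12.5% | 14.3% |
| Assumed | 0.50 | 0.750 | 25% | 33.3% |

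The first three values of r are the article's published test-retest figures. The PSI-SF figure is reported there as a Cronbach's alpha, so it is the weakest proxy.

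**2. Detectable effect at 80% power, two-sided 0.05**, in baseline SDs: 2.80 × √(2v/n), where v is 2(1 − r) for change and 1 − r² after adjustment.

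- Full sample: n = 966 × 0.9 ≈ 869 per arm. At r = 0.75 the effect goes from 0.095 to 0.089 SD.
- DPICS: about 60 per arm. At r = 0.75 it goes from 0.36 to 0.34 SD, and at r = 0.5 from 0.51 to 0.44 SD. The article gives no numerical correlation for DPICS.

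**3. Dropout.** Expected loss is 0.10 × 1932 ≈ 193 dyads. With equal SDs and no treatment effect, expected change given baseline b (in SDs) is (r − 1)b plus a constant. The bias in the regimen contrast is therefore (r − 1) times the between-arm difference in completers' baseline means.

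Suppose dropout depends on baseline in one arm only, and its dropouts start d SDs above that arm's mean. Its completers then average −d × 0.10/0.90, and the bias is (1 − r) × d × 0.10/0.90:

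- r = 0.75, d = 0.25: 0.007 SD
- r = 0.75, d = 1.0: 0.028 SD
- r = 0.50, d = 1.0: 0.056 SD

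At r = 0.75 and an assumed ECBI SD of 30–40, this is about 0.2 to 1.1 points. The article calls 10 units clinically important (Objective 5 considerations).

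A simulation of 3000 trials (966 per arm, r = 0.75, about 10% loss, intervention-arm dropout log-odds rising 0.5 per baseline SD) gave a bias of 0.012 SD for change and 0.000 for the adjusted analysis, with a variance ratio of 0.87. With the same baseline-dependent dropout in both arms, simulated bias in the change-score contrast was −0.001 SD (Monte Carlo error 0.001).

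**4. Primary model, for scale only.** The stated 80% power reproduces as 79.9%, using 20% against 13%, 966 per arm and a design effect of 1 + (9 − 1) × 0.15 = 2.2 in both arms. A baseline covariate correlated 0.1, 0.2 or 0.3 with the outcome (assumed) would raise it to 80.3%, 81.5% or 83.5%.

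**The case against.** The strongest reply is that the matter is partly handled. Baseline enters through the change score, and the constrained longitudinal model is prespecified as a check, so the dispute is about which analysis ranks first. That is fair, and it limits the point to a modest one. It does not explain why the less precise analysis should be the main one. The correlations are also only proxies: published values over 10 and 5 months, not this trial's 6–8 month correlations. That stands, and it is why a range is shown.

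A reader might infer more than the article supports:

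- **That the change-score contrast is valid only if dropout is unrelated to baseline.** It is not that strict. If dropout depends on baseline equally in both arms, the contrast is unbiased, although each arm's mean change can shift.
- **That dropout threatens the trial's main result.** The primary outcome comes from CPS record matching (Plans for assessment and collection of outcomes), so a missed interview does not remove it.
- **That any baseline adjustment recovers the 193 dyads.** Regression on baseline in completers drops the same dyads. Only the longitudinal model keeps them, and neither model corrects dropout that depends on unseen follow-up scores.
- **That the primary model is deficient without baseline BCAP.** The article gives no association between BCAP and CPS investigation, and it describes BCAP around a physical abuse scale while the endpoint is any investigation. The exploratory covariates are listed by example, so BCAP is not excluded.

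**Conclusion.** The point holds for objective 2. The main models for the secondary scores give up about 12.5% of variance for ECBI and 10% for CTS-PC, assuming equal variances at the two visits and the cited test-retest values as proxies. The loss is larger if the correlation over 6–8 months is lower, and it would matter most for DPICS.

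The completer change score is also a poor match to the ignorable-missingness assumption. The resulting bias in the regimen contrast arises only when baseline-dependent dropout differs between arms. It is about 0.03 SD or less at 10% loss and r = 0.75, for dropouts up to 1 SD from their arm's mean in one arm. This is a worthwhile improvement in efficiency and coherence. It is not a flaw that invalidates the secondary results, and it does not touch the primary outcome.

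**What to change.** **Objective 2.** Make the constrained longitudinal model the main analysis, with regimen, language and site as now, and move the raw change score to sensitivity. Specify a likelihood fit with a covariance that links the two visits. Under GEE with an independence working structure, the model would neither adjust for baseline nor use the dyads without follow-up. The minimum alternative is to add the baseline score as a covariate, which gives the precision gain but still omits dyads without follow-up.

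**Objective 5.** Baseline ECBI may be added as a covariate for the regimen contrast within each study. Baselines should not be constrained equal across studies, because randomisation does not support that, and adjustment will not remove confounding between studies.

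**Optional and minor.** Baseline BCAP could be prespecified in the primary model, reporting the standardised risk difference. With 200 cases the article's own rule allows 10 coefficients, and regimen, language and follow-up length use three. The benefit cannot be established from the documents.

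The cost is a change of wording, at most one extra coefficient per model, and no new data. It should be settled before outcomes by regimen are examined.
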